#### Inclusion criteria

According to the 7th edition of the American Joint Committee on Cancer staging, PHC is defined as a tumor originating in the common hepatic duct, the hepatic duct confluence, or in the left or right hepatic duct. [1]. The latter category may also include patients with an intrahepatic tumor that invades the hepatic duct confluence. Pathologic confirmation of PHC is not required prior to inclusion in the study. Patients are selected to potentially undergo a major liver resection if preoperative imaging with CT and/or MRCP shows a resectable tumor without evidence of distant metastases (including lymph node metastases beyond the hepatoduodenal ligament) [1]. Portal vein resection and reconstruction may be required to obtain tumor-free resection margins.

Biliary obstruction in the FLR is separately defined for patients with or without previous EBD procedures (Table 1). For drainage naïve patients, it is defined as a total bilirubin level of at least 50 μmol/L. For patients with previous EBD procedures, it is defined as a persistently rising total bilirubin level above 50 μmol/L (i.e. no stent placed or insufficiently draining stent) or as persistent biliary dilatation in the FLR on imaging (i.e. previous stent placed in contralateral side of liver).

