**Table 1 Tab1:** **Definitions of biliary obstruction in the future liver remnant**

Patient type	Definition of inadequate biliary drainage
Drainage naïve	Serum Bilirubin >50 μmol/L.
Drainage non-naïve	Persistently rising total bilirubin level above 50 μmol/L (i.e. no stent placed or insufficient draining stent).
	Persistent biliary dilatation in the FLR on imaging (i.e. previous stent placed in contralateral side of liver).

Patients are ‘drainage non-naïve’ if they underwent previous (attempted) EBD before referral to one of the enrolling centers.

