### Secondary outcome measures

Secondary outcome measures will be used to select the preferred method if there is no difference in the primary outcome at conclusion of the study. Secondary outcome measures include:The separate incidence of preoperative cholangitis;The number of drainage procedures required to achieve technical success;The proportion of patients with therapeutic success at 7 days after technical success;The total number of drainage procedures that involved (attempted) stent (re-) placement;The proportion of patients requiring crossover treatment;Interval bilirubin decrease at 7 days and 14 days after biliary drainage relative to the bilirubin level at randomization;The number of patients with rescheduled or cancelled laparotomy due to severe drainage-related complications;Quality of life, measured with the EORTC Quality of Life Questionnaire C-30 (QLQ-C30) and its biliary cancer module (QLQ-BIL21);Postoperative morbidity and mortality, as defined in Table 3, among patients who underwent combined extrahepatic bile duct and major liver resection. The International Study Group of Liver Surgery (ISGLS) definitions for post-hepatectomy liver failure, bile leakage and hemorrhage are used [14-16].

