**Flowchart of the study.**

After informed consent has been obtained, patients are randomized to undergo EBD or PTBD of the FLR within 5 days. The allocated drainage procedure should be repeated until internal biliary drainage of the FLR has been achieved (i.e. technical success). Follow-up is done at 7 days after technical success: therapeutic success at follow-up is defined as normal caliber bile ducts in the FLR on ultrasonography and a minimum 20% decrease in the total bilirubin level compared to the reference level at randomization. Additional total bilirubin assessments are performed at 14 days after technical success, and at admission for exploratory laparotomy, to evaluate patency of the biliary drainage. Revisional drainage procedures may be required if complications occur after biliary drainage, as described in Table 2. Complications are treated according to local guidelines. Crossover treatment is allowed if the allocated drainage procedure is considered to be no longer technically feasible (e.g. cholangitis with multiple isolated segments after EBD, requiring additional PTBD).

Additional staging (e.g. percutaneous biopsy or staging laparoscopy) may be used to further determine resectability of the tumor after randomization and initial biliary drainage. Patients who loose eligibility to undergo major liver resection because distant metastases are found at additional staging remain included in the intention-to-treat analysis, as described above.

Exploratory laparotomy is intentionally scheduled at 4 weeks after randomization, or at 6 weeks after randomization if the patient requires portal vein embolization. A radical resection is pursued at exploratory laparotomy if the diagnosis of resectable PHC without distant metastases is confirmed. Resections consist of excision of the liver hilum en bloc with (extended) hemihepatectomy including the caudate lobe, and complete lymphadenectomy of the hepatoduodenal ligament. Portal vein excision and reconstruction are used when necessary. If present, transhepatic percutaneous drains are left in-situ and used as transanastomotic drains to facilitate healing of the hepaticojejunostomies.

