#### Data analysis

The principal analysis consists of an intention-to-treat comparison of the number of preoperative severe drainage-related complications. The research hypothesis will be evaluated using a Wilcoxon/Mann–Whitney rank-sum test with a two-sided 0.05 significance level. The comparison will be expressed in terms of a relative risk and 95% confidence intervals, as determined with multinomial logistic regression.

Subsequent analyses are directed at the secondary endpoints. Continuous data will be presented as the mean with standard deviation or median with interquartile range depending on data distribution, and accordingly evaluated with Mann–Whitney U or t-test statistics. Categorical variables will be evaluated using Pearson’s chi-squared test or Fisher’s Exact test as applicable.

Preplanned subgroup analyses will be based on a dichotomized complication rate to retain statistical power (no complication versus 1 or more complications), and the analyses will consist of logistic regression with the subgroup and randomized treatment added as an interaction term. Subgroup analysis will be performed for patients with Bismuth type 4 tumors, and patients with a left-sided FLR.

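### The bilirubin outcomes have no baseline floor although some patients may enter without raised bilirubin, so well-drained patients can be scored as failures and the comparison of methods is diluted by an unknown amount

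*Protocol article*

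**What the plan says.** **Entry.** Inclusion criteria and Table 1 of the protocol article define biliary obstruction by three routes.

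- Drainage-naïve patients: "For drainage naïve patients, it is defined as a total bilirubin level of at least 50 μmol/L".
- Previously drained patients, first route: bilirubin above 50 μmol/L and still rising.
- Previously drained patients, alternative route: "Persistent biliary dilatation in the FLR on imaging (i.e. previous stent placed in contralateral side of liver"). The Inclusion criteria text joins it to the first with an "or" ("or as persistent biliary dilatation in the FLR on imaging"). It carries no bilirubin minimum.

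**Scoring.** Two secondary outcomes use bilirubin.

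- The interval outcome is "Interval bilirubin decrease at 7 days and 14 days after biliary drainage relative to the bilirubin level at randomization".
- Therapeutic success at 7 days after technical success is defined in the Study outline. It needs normal-calibre FLR ducts on ultrasound together with "a minimum 20% decrease in the total bilirubin level compared to the reference level at randomization".

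Neither has a baseline floor or an alternative criterion for patients who start with low bilirubin.

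**Analysis and use.** Data analysis sets the general rule for continuous secondary endpoints: "Continuous data will be presented as the mean with standard deviation or median with interquartile range depending on data distribution", tested with a t-test or Mann-Whitney U test. No baseline adjustment is mentioned. Secondary outcome measures gives these endpoints a decision role: "Secondary outcome measures will be used to select the preferred method if there is no difference in the primary outcome at conclusion of the study".

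**The concern.** The entry rule and the scoring rule do not fit each other. The dilatation route describes patients whose other liver side already drains through a stent, and their serum bilirubin may be near normal. If so, drainage of the FLR can solve the problem that qualified them (dilated ducts) but cannot lower bilirubin by much.

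Two things follow:

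- In therapeutic success, such a patient counts as a failure even with fully normal ducts, because both components are required.
- In the interval outcome, the patient contributes a change near zero plus measurement noise, whichever method was used.

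Both effects pull the arms together. If the primary outcome shows no difference, the protocol turns to the secondary outcomes to choose a method, and these two are the only listed outcomes that measure bilirubin response. A real difference in drainage efficacy could then be missed.

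**Working it through.** **What the plan computes.** The protocol gives no power, SD or expected value for the bilirubin outcomes, so there is no figure of its own to reproduce here. Its 53 per arm is for the primary outcome, and it does reproduce: a Wilcoxon test on the Table 4 proportions (two-sided 0.05, power 0.80) needs 50.8, so 51 per arm, and 51/0.97 = 52.6, so 53. The checks below use 51 evaluable patients per arm.

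**Step 1: chance that a well-drained patient with normal baseline meets the 20% rule.** If the true level does not change and each sample has coefficient of variation CV (assumed), the log ratio of the two samples has SD √2 × CV. So P(fall ≥ 20%) = Φ(ln 0.8 / (√2 × CV)), with ln 0.8 = −0.223.

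- CV 15%: Φ(−0.223/0.212) = 0.146
- CV 20%: Φ(−0.223/0.283) = 0.215
- CV 25%: Φ(−0.223/0.354) = 0.264

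About 74% to 85% of such patients are therefore scored as failures despite full drainage.

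**Step 2: simple dilution.** Let f be the share of patients with no bilirubin to lose. The overall difference between methods shrinks to (1 − f) of its value in the others, and at equal variance the required number rises by 1/(1 − f)²: 1.23, 1.56 and 2.04 for f = 10%, 20% and 30%.

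Example for a responder outcome, assuming 60% v 85% success in jaundiced patients and 0% in the rest. At f = 10% the rates become 0.60 × 0.9 = 0.54 and 0.85 × 0.9 = 0.765. Power with 51 per arm falls from 82% (f = 0) to 67%, 54% and 42% at f = 10%, 20% and 30%. With 20% success by noise in the rest it is 68%, 55% and 43%. This is the extreme case, in which every patient in the share f starts at normal bilirubin.

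**Step 3: percentage decrease, with the baseline level varied as well.** Assumptions, none of them from the protocol: jaundiced patients at a median of 200 μmol/L; bilirubin half-life 8 v 5.6 days with log-SD 0.4; day-7 value = floor + (baseline − floor) × 0.5^(7/half-life), with a floor of about 10 μmol/L; 15% noise on both samples. Mann-Whitney power on percentage decrease:

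| Bilirubin of dilatation-route patients | share 10% | 20% | 30% |
|---|---|---|---|
| about 12 μmol/L | 0.79 | 0.62 | 0.49 |
| median 30 μmol/L | 0.86 | 0.80 | 0.75 |
| median 50 μmol/L | 0.90 | 0.87 | 0.84 |

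With no such patients, power is about 0.91. Repeats with other choices of baseline spread and floor moved the first row the most, down to 0.75, 0.57 and 0.38. ANCOVA of log bilirubin on arm and log baseline kept about 0.81 to 0.93 across the scenarios in the table.

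**Step 4: is there bias?** With equal drainage in both arms, the false-positive rate of the unadjusted tests stayed near 5% (0.03 to 0.07). Under simple randomization, the between-arm difference in the share has SD √(2f(1 − f)/53), which is 6, 8 and 9 percentage points for f = 10%, 20% and 30%. That chance variation is already covered by the nominal error rate.

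**The case against.** Several points on the other side stand.

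- **Unknown size.** Only one of the three routes in Table 1 lacks a bilirubin minimum, and the protocol does not say how many patients use it. The Discussion says that most referred patients have already undergone endoscopic drainage, but that is not the same as entry on dilatation alone. Nor does the text say that these patients have normal bilirubin: someone with a raised but no longer rising level also enters by this route. The table above shows how much this matters.
- **A stronger reading fails.** A reader might infer that the bilirubin outcomes mainly measure how many non-jaundiced patients were enrolled. The documents do not support that. Depending on the assumed model, the jaundiced/non-jaundiced split explains 17% to 42% of within-arm variance at a 10% share and 35% to 60% at 30%, so it is the larger part only in some models and at the higher shares.
- **Nor is it a bias.** A reader might also infer that an imbalance in such patients would pass for a difference in drainage success. Entry route is fixed before randomization, all these patients are non-naïve, and naïve/non-naïve status is a minimization factor. Step 4 shows no excess of false positives.
- **Adjustment could sit in an analysis plan.** The t-test and Mann-Whitney rule is a general default in a condensed article, and an endpoint-specific model may be specified elsewhere. The interval outcome may also mean an absolute rather than a percentage fall; a patient near normal has little room to fall on either scale.

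What the objection does not remove is the therapeutic success definition. The article states it in full, and it counts a well-drained patient with low baseline bilirubin as a failure.

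**Conclusion.** The concern holds as a mismatch between an entry route without a bilirubin minimum and two outcomes that require or measure a fall in bilirubin. For therapeutic success, patients who start near normal and are fully drained are misclassified about 74% to 85% of the time, given a CV of 15% to 25%. For the comparison of methods, the consequence is lost sensitivity, and the documents do not fix its size. Under the assumed effects it runs from slight (0.91 to about 0.90 at a 10% share and a median of 50 μmol/L) to severe (0.49 or lower at a 30% share and about 12 μmol/L). Both the share and the baseline level are assumptions.

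The problem touches two of nine secondary outcomes and leaves the primary power calculation as it is. It is still worth correcting, because the protocol lets these outcomes decide the preferred method when the primary does not.

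**What to change.** 1. Analyse log bilirubin at day 7 and at day 14 by ANCOVA on arm and log bilirubin at randomization, reported as a ratio of geometric means.
2. For the secondary endpoint of therapeutic success, apply the 20% component only to patients at or above 50 μmol/L at randomization, the trial's own cut-off. Score patients below it on FLR duct calibre.
3. Report both outcomes by entry route, so that the share of dilatation-route patients and their baseline bilirubin become visible.
4. State that this changes endpoint scoring only. Table 2 uses the same term: stent or catheter dysfunction counts only after therapeutic success was first obtained, and that event belongs to the primary outcome. Say whether Table 2 keeps the Study outline definition or takes the re-scored one, so that one term does not carry two unstated meanings.

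The cost is a few sentences and no new data, since bilirubin at randomization and the ultrasound are already collected. The small downside is a success criterion that differs by baseline bilirubin group. Item 4 needs a deliberate decision, because it touches a component of the primary outcome.

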### Primary outcome measure

The primary outcome is the total number of severe drainage-related complications measured between randomization and exploratory laparotomy. The study is designed to detect superiority of PTBD. Some patients lose eligibility to undergo major liver resection before exploratory laparotomy (e.g. distant metastases found at staging laparoscopy, deterioration of the patients’ condition, or diagnosis of benign disease precluding the need for surgical therapy). For these patients, the number of drainage-related complications is measured until 7 days after the decision to cancel exploratory laparotomy, or until 90 days after randomization (whichever comes first).

A severe complication is defined as any complication related to the drainage procedures, leading to an additional invasive intervention, (extended) hospitalization, or death. Definitions for potential severe drainage-related complications, as evaluated in previous studies, [11,13] are shown in Table 2.

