**Table 3 Tab3:** **Definitions of postoperative morbidity and mortality**

Event	Criteria
**Postoperative mortality**	Any reason of death within 90 days after major liver resection.

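### The only mortality outcome is confined to resected patients, a group formed after randomisation, yet it can help choose the preferred drainage method

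*Protocol article*

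**What the plan says.** All references are to the Protocol article.

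- **Population.** The last item under Secondary outcome measures is "Postoperative morbidity and mortality, as defined in Table 3, among patients who underwent combined extrahepatic bile duct and major liver resection".
- **Mortality.** The criterion in Table 3 is "Any reason of death within 90 days after major liver resection". It is the only item in the outcome list that measures death as such.
- **Death in the primary outcome.** Under Primary outcome measure, a severe complication is "any complication related to the drainage procedures, leading to an additional invasive intervention, (extended) hospitalization, or death". Death enters only as the consequence of a complication related to drainage.
- **Primary window.** For patients who reach surgery, "The primary outcome is the total number of severe drainage-related complications measured between randomization and exploratory laparotomy". For those who lose eligibility first, counting runs "until 7 days after the decision to cancel exploratory laparotomy, or until 90 days after randomization (whichever comes first").
- **Reasons for losing eligibility.** The examples given are "distant metastases found at staging laparoscopy, deterioration of the patients’ condition, or diagnosis of benign disease precluding the need for surgical therapy".
- **Use of the secondary outcomes.** The opening sentence of Secondary outcome measures says that they will decide which method is preferred if the primary outcome does not differ between arms.
- **Analysis principle.** Statistical analysis bases the analysis on intention to treat.

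**The concern.** Resection happens after randomisation, and the assigned drainage can change who gets there. The article supplies both links itself: Background says that drainage complications can worsen the patient's condition, and Primary outcome measure names deterioration as a reason for cancelling laparotomy. A comparison among resected patients is thus not protected by randomisation and does not follow the intention-to-treat principle stated for the analysis.

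The direction of the possible error matters. If one drainage method costs more patients their lives or their fitness before surgery, those lost are likely to be the frailer ones. The patients left for resection in that arm are then a fitter selection.

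This would matter less if the postoperative results were only described. But the article gives the secondary outcomes a deciding role when the primary is null. In that situation the plan offers no unbiased mortality comparison to set beside the others.

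**Working it through.** **1. Where a death is counted.** Following each pathway through the definitions:

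| Death | Primary count | Table 3 mortality |
|---|---|---|
| Before laparotomy, from a complication judged drainage-related | one event | no |
| Before laparotomy, not judged drainage-related | none | no |
| After cancellation, from a drainage-related complication inside the window | one event | no |
| After cancellation, from a complication arising after the window | none | no |
| After laparotomy without resection, from a complication arising after laparotomy | none | no |
| Within 90 days after resection | none | yes |

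Three of the six rows enter neither. In the two rows that reach the primary, a fatal complication has the same value as one stent dysfunction.

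**2. The denominator.** Sample size gives 53 per arm, and this reproduces. From Table 4, P(EBD > PTBD) + ½P(tie) = 0.4175 + ½ × 0.4375 = 0.636. The rank-sum formula with tie-corrected null variance and alternative variance, two-sided 0.05 and power 0.80, gives 50.8, so 51 per arm. Then 51 / 0.97 = 52.6, so 53. The present point does not alter this number.

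**3. A simple case (assumed counts).** With 5 deaths before resection in one arm and 0 in the other, the difference is 5/53 = 9.4 percentage points. Table 3 mortality records none of these deaths.

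**4. A fuller illustration.** The inputs below are assumptions, except the 18%, which is the highest postoperative mortality quoted in Background.

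- d = risk of death before surgery: 5% in the EBD arm, 15% in the PTBD arm. The labels are arbitrary, and swapping them gives the mirror image.
- r = share of survivors resected: 40% to 70%.
- m = postoperative mortality: 18% in both arms.
- No deaths among unresected survivors, which understates what is missed.

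Table 3 mortality is then 18% v 18%. All-cause mortality from randomisation to 90 days after resection is d + m(1 − d)r:

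| r | EBD | PTBD | PTBD deaths outside Table 3 |
|---|---|---|---|
| 0.40 | 0.05 + 0.18 × 0.95 × 0.40 = 11.8% | 0.15 + 0.18 × 0.85 × 0.40 = 21.1% | 0.15/0.211 = 71% |
| 0.70 | 0.05 + 0.18 × 0.95 × 0.70 = 17.0% | 0.15 + 0.18 × 0.85 × 0.70 = 25.7% | 0.15/0.257 = 58% |

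A difference of about 9 points appears as none. With d = 5% in both arms, 42% (r = 0.40) to 29% (r = 0.70) of deaths still fall outside Table 3.

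**5. Why the arm with more losses can look better, not merely equal.** Mortality among resected patients is a weighted average of a higher risk in frail patients and a lower risk in fit ones. Losing more frail patients before surgery lowers their weight, so the average falls with no change in surgical outcome.

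**6. Precision.** For 21.1% v 11.8% with 53 per arm, the standard error is √(0.118 × 0.882/53 + 0.211 × 0.789/53) = 0.072. The 95% CI is 9.3 ± 14.0 points. An all-cause comparison would be imprecise; what it gains is an unbiased contrast.

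**The case against.** The case on the other side is substantial, and most of it stands.

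- **Most severe drainage-related harm before surgery is counted.** Complications leading to intervention, hospital stay or death are in the primary. A blinded committee adjudicates them, and patients found to have metastases at additional staging stay in the intention-to-treat analysis. A reader might infer that preoperative harm in general goes uncounted; the documents do not support that. What escapes is death not attributed to drainage and events after the cut-off.
- **Other outcomes touch on the gap.** Laparotomy rescheduled or cancelled because of severe drainage complications is a secondary outcome. The DSMB sees unblinded serious adverse events at 53 patients, and the review board receives annual reports by group. But the first depends on attribution to drainage, and the others are safety monitoring. Neither gives a mortality comparison for the choice of method.
- **The 7-day rule is defensible.** A reader might infer that it systematically shortens observation of cancelled patients. Operated patients stop at laparotomy, planned at 4 weeks, or 6 with portal vein embolisation. Against day 28, cancellation after day 21 gives a longer window (21 + 7 = 28). Counting cancelled patients to day 90 would give them 90/28 = 3.2 times the observation of a patient operated on at day 28, a larger imbalance than the one it would cure.
- **Ranking every preoperative death worst** might also seem to follow. It would bring cancer deaths into an outcome meant to count drainage complications, and so change the question.
- **Therapeutic success** is timed from technical success, but how technical failures enter its denominator is a detail an article may leave to the full protocol.
- **A postoperative outcome omits preoperative deaths by definition.** True, and as a description it is sound. The difficulty lies in its being the only mortality outcome and in its role in the decision.

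**Conclusion.** The point holds for the mortality outcome and for the use of the resected-only results in choosing a method. The primary hypothesis, its test and the sample size are not affected, and only one of the nine secondary items is restricted to resected patients. It is a worthwhile correction to the secondary outcomes, not a defect that invalidates the trial.

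Its size cannot be taken from the documents, because they give no preoperative death rate or resection rate. Under the assumptions shown, a true difference of about 9 percentage points in all-cause mortality would appear as 18% v 18%, and 58% to 71% of deaths in the worse arm would lie outside the mortality outcome. Bias between arms requires that the arms differ in who is lost before resection. The article's own account makes this plausible but does not establish it.

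**What to change.** - **Add** all-cause mortality from randomisation to a fixed time in all randomised patients, by intention to treat, with a risk difference and 95% CI. State that this is the mortality comparison used when the secondary outcomes decide the preferred method.
- **Report** postoperative morbidity and mortality among resected patients as descriptive and non-randomised, next to the number resected per arm out of all randomised.
- **Leave** the primary count and its 7-day rule unchanged.

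Day 90 is convenient: a questionnaire is already scheduled then (Data collection and monitoring), and serious adverse events are already reported by group (Safety). One trade-off should be settled openly. With laparotomy at day 28 or 42, day 90 covers 62 or 48 postoperative days. A horizon of 42 + 90 = 132 days would cover the full Table 3 period for patients operated on schedule, at the price of one later check of vital status.

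The cost is outcome wording and confirmation of vital status for every randomised patient. The small downside is that disease-related deaths add noise.
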